### Treatments

#### ACT

Participants randomised to the ACT condition are offered eight 50-minute sessions of ACT, delivered at weekly to fortnightly intervals within a time frame of around three months. We considered that an eight-session intervention would provide a more comprehensive treatment for our chronically affected sample than that offered in the two trials with acute inpatients, but would nevertheless remain much briefer than trials of CBTp, which average 20 sessions in length [35], and our combined ACT-CBT TORCH protocol of 15 sessions [38]. ACT is conducted according to a local manual which is largely based on the first edition of the ACT manual [29] but with recommended adaptations for psychosis [34,57]. The 8 sessions comprise an initial assessment session followed by 7 intervention sessions. The initial session includes an orientation to therapy and an assessment of symptoms and problems related to psychosis. During this session, the therapist also notes the participant’s degree of struggle with symptoms and motivation for change as basic indicators of the most useful starting point for subsequent interventions. For example, creative hopelessness, the traditional beginning to ACT, is likely to be most suitable for clients who have struggled with their symptoms and are highly motivated to change. For clients who are less motivated or ambivalent about therapy it may be more useful to start with a focus on values and goals. While guidelines are provided, the therapist is expected to tailor the components according to the needs of the participant as identified in the assessment phase. The order in which these intervention components are delivered is also left to the therapist’s judgment. Participants are provided with folders for handouts and sessions are recorded onto CDs for home review.

### Measures

#### Outcome measures

##### Overall mental state

Overall impact upon mental state is measured by the Positive and Negative Syndrome Scale (PANSS - [55]), a widely-used, comprehensive interview-based measure of schizophrenia symptomatology which consists of seven items measuring positive symptoms, seven items measuring negative symptoms and 16 items measuring general symptoms. We will report overall mental state (as measured by the total score) along with subscale scores.

##### Positive symptoms

The Psychotic Symptom Rating Scales (PSYRATS - [41]) is a semi-structured interview designed to assess the severity of an individual’s auditory hallucinations and delusions across a range of physical and psychological dimensions. We use items from the PSYRATS to assess the severity of hallucinations and delusions according to the specific dimensions of interest to the study which include preoccupation, conviction, distress and disruption to life. In order to be able to control for the presence and frequency of symptoms, the frequency dimension of the PSYRATS auditory hallucinations subscale and the amount of preoccupation dimension of the PSYRATS delusions subscale is also be assessed. This scale has good psychometric properties and excellent inter-rater reliability across both scales is excellent, ranging from 0.788-1.00 for hallucinations and 0.884 – 1.00 for delusions [41].

Delusions are further assessed using the Peters Delusions Inventory (PDI - [43]). This self-report measure assesses delusional thinking more broadly and has been found to be a reliable and valid of delusional thinking in the general population and to discriminate between clinical and non-clinical samples on conviction, preoccupation and distress [43]. Participants are asked to indicate the presence or absence of 21 delusional beliefs (e.g., “Do you ever feel as if people are reading your mind?”) giving a total score of 0–21. Each delusional belief endorsed is then rated on dimensions of preoccupation, conviction and distress. The total number of items endorsed on the PDI will be used to assess for any paradoxical increases in symptom reporting.

##### Social functioning

Impact on overall social functioning is assessed with the Social Functioning Scale (SFS - [61]). This is a comprehensive interview-based assessment for individuals with schizophrenia that assesses seven areas of functioning essential to living in the community (social engagement, interpersonal behavior, prosocial activities, recreation, independence and employment). It has been shown to be valid, reliable, and sensitive to change [61]. This is completed on the basis of interview with the participant and discussion with their case manager or alternative informant. The Sheehan Disability Scale (SDS - [62]) is a 3-item self-report instrument measuring impairment and functional disability due to psychiatric symptoms across key domains of work/education, social life and family life/home responsibilities. Responses are measured on a 10-point partially anchored visual analogue scale from 0 (not at all) to 10 (extremely) and assessed over the last month.

##### Adaptive behavior

Direct impact on behavior is assessed using a time budget measure for schizophrenia [63] which calculates the level of adaptive activity undertaken by the participant over a representative week on the basis of a detailed interview. Level of adaptive activity is rated from 0: nothing – lying thinking sleeping sitting etc. to 4: time period filled with a variety of demanding independent activities requiring significant motivation and planning and with some variation in tasks, e.g., work. Four time blocks per day are rated over 7 days with the total weekly score ranging from 0 – 112. It has been used successfully with schizophrenia, with good reliability and validity [63]. The specific hypothesis that treatment will moderate the impact of negative symptoms will be assessed using the PANSS Negative Syndrome subscale.

##### Service utilisation

Service utilisation during the follow-up period will be compared with baseline rates of service utilisation using a subset of self-report questions extracted from instrumentation as used in the previous (2007) Australian National Survey of Mental Health and Wellbeing. Forms of service use include both psychiatric hospital admissions (number and days) and consultations with mental health service providers (number and length). This broader measure of service use is used in preference to rehospitalisation rates alone, due to the relatively low baseline rate of readmission in a chronic sample. Indeed, Gumley et al. [64] estimate a sample size of over 400 participants would be required to detect changes in readmission rates, which was not feasible in this study.

#### Process measures

##### Acceptance and commitment

The 16-item Acceptance and Action Questionnaire (AAQ - [65]) is used in order to measure the hypothesised therapy mechanisms of (a) increasing the degree of acceptance of psychotic experiences as opposed to attempted suppression and experiential avoidance, and (b) increasing commitment to valued action. Like the more commonly used 9-item AAQ, this version has single factor structure. It was chosen on the basis of the authors’ view ([58], p. 563) that in a research context the additional items were likely to confer greater sensitivity to change. (The present study was devised prior to publication of the AAQ II [66]). Internal consistency of the 16-item version was not reported however it correlates .89 with the 9-item version which has a Cronbach alpha of .70. Extensive convergent and divergent validity has been reported with versions of the measure widely used in research on the mechanisms of ACT [32,65]. As this measure has not been previously applied to psychosis, our group has previously developed a measure for auditory and command hallucinations that directly taps each construct (the Voices Acceptance and Action Scale – VAAS), with promising initial results and acceptable psychometric properties [67]. The VAAS is used in addition to the AAQ for participants experiencing auditory hallucinations.

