**Figure 1 F1:**
[figure not shown]
Hypothesised mechanisms of action for ACT.

Our hypotheses are therefore that, compared to patients receiving equivalent clinician time, patients who receive ACT will show improvement in (a) overall mental state (incorporating positive, negative and general symptoms); (b) preoccupation, conviction, distress and disruption to life associated with positive psychotic symptoms; (c) social functioning, and (d) adaptive behavior. Outcomes will also be examined in relation to (e) service utilisation. We hypothesise that all changes will be achieved by the conclusion of therapy and maintained at six-month follow-up. The study will also examine hypothesised mechanisms of action, namely that within the ACT group (f) improvements in positive symptoms will be predicted by reductions in experiential avoidance, (g) improvements in negative symptoms will be predicted by increased commitment to action and (h) if any paradoxical increase in the number of symptoms are reported, this will be mediated by recovery style. Finally, we considered that cognitive impairments commonly seen in schizophrenia [51-53] could interfere in understanding abstract metaphors and retaining information in the ACT condition, thereby moderating outcomes. The inclusion of several cognitive measures as covariates, including verbal memory, abstract reasoning and premorbid IQ, will allow us to examine the role of cognitive functioning on outcome.

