### Statistical analysis

The primary focus of the analysis is differential changes in the ACT group versus Befriending from baseline to endpoint, which will be analysed within the framework of Treatment Group (ACT vs. Befriending) by Measurement Occasion (baseline, endpoint, follow-up) design. Analyses will be undertaken using mixed-model repeated measures (MMRM) which is the recommended method for examining clinical trial data [75]. Primary evidence of the efficacy of ACT will be a significant two-way interaction demonstrating greater change in outcome measures in the ACT group from pre- to post-therapy. Baseline to follow-up interactions with treatment group will also be examined. Where there are significant group x time interactions, planned contrasts will compare changes from baseline under each intervention at endpoint and follow-up.

Intention-to-treat (ITT) analysis [76] will be used. MMRM is well-suited to ITT analyses because this approach uses all available information from subjects as randomised to produce ITT estimates of treatment effects under only mild assumptions concerning the nature of withdrawal [75]. Most importantly, subjects with incomplete data are not discarded and missing data are not replaced with unprincipled estimated values or observations carried forward [77]. This approach is regarded as the most appropriate method of analysing RCT data by the highest quality journals, which have adopted the CONSORT standard (see, e.g., [78]). However, if data are grossly non-normal and cannot be successfully transformed, non-parametric methods will be used.

The mediational impact of pre to post AAQ, RSQ and medication dose change will be assessed using the Sobel test [79], arguably the most powerful current method of detecting indirect effects [80]. This test assesses the statistical significance of the product of the coefficients for treatment-mediator and mediator-outcome effects. A bootstrapped multivariate extension of the Sobel test described by Preacher and Hayes [81,82] will be used, which is suitable for non-parametric data, and allows us to examine both the total indirect effect and the individual effect of each specified mediator, controlling for the other.

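### Hypotheses (f) and (g) name two different mechanisms, but the only named mediator bearing on either is the AAQ, which the article describes as single-factor

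*Protocol article*

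**What the plan says.** Under Aim, hypothesised outcomes and mechanisms of change, the protocol article sets out two mechanism hypotheses within the ACT group. Hypothesis (f) is that "improvements in positive symptoms will be predicted by reductions in experiential avoidance". Hypothesis (g) is that "improvements in negative symptoms will be predicted by increased commitment to action". The text introducing Figure 1 draws the same two paths: acceptance and defusion act on positive symptoms, and committed action works through behavioural change on negative symptoms.

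Under Process measures, Acceptance and commitment, one instrument receives both tasks: "The 16-item Acceptance and Action Questionnaire (AAQ - [65]) is used in order to measure the hypothesised therapy mechanisms of" (a) greater acceptance in place of suppression and avoidance, and "b) increasing commitment to valued action". The next sentence reads: "Like the more commonly used 9-item AAQ, this version has single factor structure". No AAQ subscales are described. A second scale, the VAAS, is presented as addressing each of the two constructs directly, but for a limited group: "The VAAS is used in addition to the AAQ for participants experiencing auditory hallucinations".

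Under Statistical analysis: "The mediational impact of pre to post AAQ, RSQ and medication dose change will be assessed using the Sobel test". A bootstrapped multivariate extension is to give the effect of each mediator adjusted for the others. The VAAS is not named there.

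**The concern.** The hypotheses treat avoidance and commitment as two variables, each with its own outcome. The measurement section provides a single dimension for both. If one AAQ change score stands for avoidance in (f) and for commitment in (g), the label on the result comes from the hypothesis and not from the data.

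What is at stake is interpretation of the mechanism results. The abstract says that the model of change behind ACT will be tested by mediation analysis. An association between AAQ change and negative symptoms could be reported as support for the commitment path when it may reflect acceptance, or a general process covering both.

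**Working it through.** This is mainly a consistency check, so the statements are set side by side first.

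| Element | Hypothesis (f) | Hypothesis (g) |
|---|---|---|
| Outcome | positive symptoms | negative symptoms |
| Stated predictor | experiential avoidance | commitment to action |
| Instrument assigned (all participants) | AAQ | AAQ |
| Stated structure of the instrument | one factor | one factor |
| Named mediator bearing on it | AAQ | AAQ |

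Of the other two named mediators, the RSQ serves hypothesis (h) on recovery style, and medication dose change is a rival explanation. That leaves the AAQ alone for (f) and (g).

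**What one score can and cannot show.** Let M be AAQ change, and P and N the changes in positive and negative symptoms. The data give two associations, M with P and M with N. These can differ: M may predict P and not N, or the reverse, or neither. What would separate the mechanisms is a model with two process variables, A (acceptance) and C (commitment), entered together. The variance inflation from entering two scores with correlation r is 1/(1 − r²). It is 1.33 at r = 0.5, 2.78 at r = 0.8 and 5.26 at r = 0.9, and has no finite value at r = 1, which is the case when A and C are the same score. Adjusting each mediator for the others therefore cannot separate the two.

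**The plan's own sample size.** The Sample size section gives 53 per arm for d = 0.55, 80% power and α = 0.05. A two-sided normal approximation gives 52. The two-sample t-test gives 52.87, hence 53, with power 0.801 at 53. The figure reproduces and does not change under this point. It is used below only as the size of the ACT arm.

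**Size of a separable test with the VAAS.** The eligibility criteria require a score of 4 or more on PANSS P1 and/or P3, so delusions alone can qualify and the VAAS need not cover everyone. The share of voice-hearers is not given. I assume 50% to 80%:

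- 0.5 × 53 = 26.5, about 27
- 0.8 × 53 = 42.4, about 42

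The denominator is 53 and not 106, because (f) and (g) are stated within the ACT group.

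**Precision.** The smallest simple correlation detectable with 80% power at two-sided α = 0.05 is tanh[(1.960 + 0.842)/√(n − 3)]:

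- n = 53: tanh(2.802/√50) = 0.38
- n = 42: tanh(2.802/√39) = 0.42
- n = 27: tanh(2.802/√24) = 0.52

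These figures assume complete data and one predictor. Entering two correlated scores together would usually need stronger associations.

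**The case against.** The strongest objection is that the analysis section may not be the analysis of (f) and (g) at all. Those hypotheses are worded as prediction within one arm. The Sobel approach multiplies a treatment-to-mediator effect by a mediator-to-outcome effect and so needs both arms. The within-ACT model is not spelled out, and an article may leave it to a fuller document. This stands as a caution against reading the list of mediators as exhaustive. It does not remove the conflict, because the measurement section itself gives both constructs to the AAQ and calls it single-factor. A fuller document could define AAQ item subsets, but that statement gives them no support, and the article notes that internal consistency of the 16-item version was not reported.

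Three stronger readings are tempting and are not supported:

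- *That no result could favour (f) over (g).* A reader might infer this from the shared score. It is wrong: AAQ change may predict one outcome and not the other. What is lost is attribution to a distinct mechanism.
- *That the VAAS is collected and then left unused.* The article lists it among the process measures, and the Procedure section has these assessed at all three time points. Its absence from one sentence does not show that it will go unanalysed.
- *That the VAAS certainly supplies the two scores needed.* The article says that it addresses each construct, but describes no subscales or separate scoring. It is also a voice-specific scale, so whether it captures commitment to action in general is not established.

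It is also fair to say that the time-budget measure of adaptive behaviour, collected in everyone, bears on the commitment path. It measures the behaviour expected to follow from commitment, and not commitment itself.

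**Conclusion.** The point holds as an internal conflict between the mechanism hypotheses and the instrument assigned to them, and not as a gap in detail. As written, AAQ results can show whether one general process relates to positive symptoms, negative symptoms, both or neither. They cannot show that acceptance drives the first and commitment the second.

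The size is modest. Neither the primary outcome (PANSS total) nor its group-by-time test is affected, so this should be corrected but does not threaten the main result. A separable test, if the VAAS permits one, would rest on about 27 to 42 participants in the ACT arm and would detect only simple correlations of roughly 0.4 to 0.5 with 80% power. Those figures depend on the assumed 50-80% share of voice-hearers and on complete data. The conflict itself depends on neither.

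**What to change.** 1. Reword (f) and (g), or the statement of how they will be tested, so that whole-sample AAQ results are reported as one general acceptance/psychological-flexibility process related to positive and to negative symptoms, and not as evidence for two separate paths.
2. Name the VAAS in the process analysis for participants with auditory hallucinations. If the sponsor confirms that the scale yields separate acceptance and action scores, use the first for (f) and the second for (g). If it does not, make no claim of separate paths.
3. Label the VAAS analysis exploratory, and settle the choice of scores before the data are analysed, so that the score counted as commitment is not picked afterwards.

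The cost is wording and one extra analysis, with no new data collection. The drawback is that the separable test covers only voice-hearers in the ACT arm, is imprecise, and may not extend to participants with delusions alone.

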##### Recovery style

The Recovery Style Questionnaire (RSQ - [68]) is used to assess the degree to which participants ‘integrate’ their illness, acknowledging their illness experiences with interest and curiosity (e.g., “I can see positive aspects to my illness”; “My illness is part of me”), as opposed to ‘seal over’ whereby participants seek to encapsulate their psychosis as separate from themselves and express disinclination for any exploration of their illness experiences (e.g., “My illness has had little effect on my life”; “I’m not really interested in my illness”). This self-report scale has 39 items; higher scores indicate greater sealing over. The RSQ has been evaluated as a valid measure of recovery style according to the original concept [49,69]. It has been found to have high test-retest reliability (Spearman 4 = 0.81) and an acceptable Cronbach’s alpha of 0.73 [68].

#### Covariates

##### Premorbid IQ

The WTAR is administered as a test of premorbid IQ. Participants are asked to read a list of 50 words that have atypical grapheme to phoneme translations (e.g., “liaison”, “ paradigm”) and are scored according to accuracy of pronunciation (raw score range 0–50). WTAR raw scores are standardised based on age then converted to the predicted WAIS-III IQ. While predicted IQ scores will be reported descriptively, these are associated with very large confidence intervals; standardised scores will therefore be used for analyses due to their greater precision.

##### Abstract verbal reasoning

The Similarities subscale of the Wechsler Adult Intelligence Scale III (WAIS-III) [70] is administered to assess abstract verbal reasoning in relation to concept formation. The subscale consists of 19 items: participants are asked to describe how two given things are alike (e.g., “table and chair”, “poem and statue”). Raw scores are converted to age-adjusted scaled scores using the normative data provided in the manual.

##### Verbal memory

The Story Memory and Story Recall subtests of the Repeatable Battery for the Assessment of Neuropsychological Status (RBANS) [71] are used to assess immediate and delayed memory. Story Memory involves reading a brief story and asking the participant to repeat it back immediately. It is scored over two trials (total score 0–24). Story Recall involves free recall of the story after a delay of 15–20 minutes (total score 0–12). Raw scores will be converted to z scores for analyses using normative data for each participant’s age group [72].

##### Antipsychotic medication

Antipsychotic medication changes and dosages are tracked at each assessment point and will be converted to chlorpromazine-equivalent dosages [73]. Chlorpromazine-equivalent dosages will be compared between groups in order to verify whether groups are equivalent, and correlations will be examined between dosage changes during the study period and clinical outcomes in order to exclude the possibility that medication changes are responsible for outcome.

#### Therapy evaluation

At the end of their post-therapy assessment, participants are asked to complete the Client Satisfaction Questionnaire-8 (CSQ-8 - [74]) to assess the acceptability and experience of therapy. As well, four additional questions give participants an opportunity to provide more specific feedback about their experience of therapy. These include ratings of emotional response and problem improvement with respect to problems related to psychosis and qualitative feedback related to therapy gains and disappointments. We expect that therapy will be rated positively by a majority of patients.

#### Treatment fidelity

Treatment sessions are audio recorded and a stratified random sample of audio files will be rated by an independent assessor for compliance with therapy condition. The assessor, blinded to treatment condition, will be required to assign each audio file to either ACT or Befriending. Because no validated scale currently exists to measure therapist adherence to ACT guidelines more specifically, an ACT fidelity scale is developed in the initial phase of the trial. The Befriending Treatment Integrity Measure [58] is used to assess the quality of Befriending sessions and to ensure that ACT sessions do not include Befriending techniques.

